### **7.1.2 STANDARD OF CARE STUDY PROCEDURES**

The trial will be implemented as per the National PrEP framework.

HTC provided at the workplace is standard of care based on national guidelines [24]. Standard HTC includes pre-test counselling, a finger-prick based, a rapid HIV test (followed by a second confirmatory test with a second test type should the first test prove positive), and post-test counselling. Individuals who test positive for HIV will be linked to HIV care and treatment services at a local HIV Care and Treatment Clinic (CTC).

## **7.2 Laboratory Procedures/Evaluations**

All individuals willing to participate in screening will receive rapid HIV testing and counselling according to national guidelines [24]. Blood for Hepatitis B and baseline creatinine testing will be collected and sent to a local accredited laboratory at MUHAS, which will adhere to Good Clinical Laboratory Practice (GCLP) standards. Follow-up testing will occur as shown below.

| Visit                           | Onsite workplace test                  | Local laboratory test                                                |
|---------------------------------|----------------------------------------|----------------------------------------------------------------------|
| Recruitment and screening visit | HIV rapid test                         | Hepatitis B surface antigen test
Creatinine test
Syphilis test |
| Month 1                         | HIV rapid test                         |                                                                      |
| Month 2                         | TDF urine assay test                   |                                                                      |
| Month 4                         | HIV rapid test                         |                                                                      |
| Month 6                         | HIV rapid test
TDF urine assay test | Hepatitis B surface antigen test
Creatinine test
Syphilis test |

### 7.3. Study Schedule

#### 7.3.1 SCREENING

##### Recruitment and Screening visit

- Recruitment of barmaids for screening and PrEP intervention
- Obtain informed consent of potential participant verified by signature on screening informed consent form.
- Conduct screening questionnaire.
- Obtain demographic information and medical, medication, alcohol and tobacco use history.
- Review medical history to determine eligibility based on inclusion/exclusion criteria.
- Review medications history to determine eligibility based on inclusion/exclusion criteria.
- Perform medical examinations needed to determine eligibility based on inclusion/exclusion criteria. Specifically we will perform:
  - A point-of-care HIV test as part of standard HIV counselling and testing;
  - A point-of-care Hepatitis B surface antigen (HBsAg);and
  - Blood sample collection for a local, laboratory-based test of serum creatinine and syphilis.
- Schedule study visits for participants who are eligible and available for the duration of the study.

- The screening visit will require between 1.5 and 2 hours to complete

---

### **7.3.2 ENROLLMENT/BASELINE**

#### **Baseline Visit (Visit 0, Month 0)**

- Obtain informed consent of potential participant verified by signature on study informed consent form.
- Verify inclusion/exclusion criteria.
- Division into the two study randomization groups 1 and 2
- Directly observe the first dose of emtricitabine/tenofovir disoproxil being taken and provide 28 (1 month) days of emtricitabine/tenofovir disoproxil.
- Counsel participant on adherence to emtricitabine/tenofovir disoproxil and need to contact the study if any changes in health arise.
- Conduct baseline questionnaire

---

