#### 4.3.1 PRIMARY ENDPOINT

**Initiation on PrEP measured by the proportion of those offered PrEP who are directly observed to initiate PrEP.** The first primary objective of this study is to determine whether offering immediate, on-site PrEP initiation raises initiation rates relative to a peer-navigator led, facility-based initiation process. This endpoint will measure whether the workplace-based initiation process improves uptake, and thus improves the ability of PrEP programs to protect those at high risk of HIV acquisition.

**Adherence to PrEP measured by urine drug level at 6 months post-enrollment.** The second primary objective of this study is to determine PrEP initiation and drug refill at women's workplaces will improve adherence to PrEP treatment. Measuring adherence to PrEP using urine drug level is the most precise and direct way to measure adherence in the recent past, and thus whether the participant is currently using the drug. Self-report of PrEP use is likely to be biased by social desirability. Ongoing adherence to PrEP is vital to maintaining the protective effect of ART against HIV infection. The primary endpoint will be measured across the two delivery method groups: facility-based and workplace-based PrEP delivery. Women who default from PrEP treatment or are lost to follow up will be assumed to have zero TDF in their urine.

**Thesis;** this will be a qualitative study that will document Barmaids' preferences, willingness to use, factors influencing uptake of long-acting injectable HIV PrEP and feasibility of implementing injectable PrEP.

---

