#### 6.1.2 FORMULATION, APPEARANCE, PACKAGING, AND LABELING

Emtricitabine/Tenofovir disoproxil Mylan is available as a light green, film-coated, capsule shaped, biconvex tablet, of dimensions 19.80 mm x 9.00 mm, debossed with 'M' on one side of the tablet and 'ETD' on the other side. It is available either as a bottle or blister pack of 30 film-coated tablets. Emtricitabine/Tenofovir disoproxil Mylan is manufactured by Mylan Inc. and its subsidiary Matrix Laboratories Limited, and has been judged bioequivalent to Truvada. Emtricitabine/Tenofovir disoproxil Mylan is a commercially marketed product, and is available for humans in the form, route and dose planned in this trial.

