### **6.1.5 DOSING AND ADMINISTRATION**

Emtricitabine/Tenofovir disoproxil will be dosed as a single tablet (containing 200 mg/300 mg of emtricitabine and tenofovir disoproxil fumarate) once daily taken orally with or without food.

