### **7.3.3 FOLLOW-UP**

#### **Refill Visit 1 (Visit 1 Day 30 +/- 7; Month 1)**

- Provide additional 28-days (1 month) supply of medication to the participant
- Check on adverse effects
- Adherence Counselling
- Test for HIV

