#### **Refill Visit 3 (Visit 5, Day 150 +/- 7; Month 5)**

- Provide additional 28-days (1 month) supply of medication to the participant
- Check on adverse effects
- Adherence Counselling

---

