### **7.3.4 FINAL STUDY VISIT**

#### **Final Study Visit (Visit 6, Day 180 +/- 7; Month 6)**

- Record adverse events as reported by participant or observed by investigator.
- Record vital signs or other health conditions.
- Collect blood for creatinine and syphilis testing.
- A point-of-care Hepatitis B surface antigen (HBsAg)
- Collect urine for TDF testing for adherence

- Test for HIV
- Record participant's adherence to treatment regimen.
- Provide additional 28-days (1-month) supply of medication to the participant
- Provide final HIV prevention counselling to participant.
- Conduct endline questionnaire
- Inform of continued follow-up support to care by the national program
- Visit 6 will require between 1.5 and 2 hours to complete

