| Syphilis testing                                            | X                               |                  |                  |                     |                  |                     |                  | X                           |
| HBsAg test                                                  | X                               |                  |                  |                     |                  |                     |                  | X                           |
| Serum creatinine test                                       | X                               |                  |                  |                     |                  |                     |                  | X                           |
| HIV test                                                    | X                               |                  | X                |                     |                  | X                   |                  | X                           |
| Schedule study visits                                       | X                               |                  |                  |                     |                  |                     |                  |                             |
| Provide 28 days of emtricitabine/tenofovir disoproxil       |                                 | X                | X                | X                   | X                | X                   | X                | X                           |
| Randomization 2 (Omni-channel PrEP Champion)                |                                 | X                |                  |                     |                  |                     |                  |                             |
| Record vital signs                                          |                                 |                  |                  | X                   |                  | X                   |                  | X                           |

| Procedures                                        | Recruitment and Screening Visit | Baseline Visit 0 | Visit 1 (refill) | Follow-up (Visit 2) | Visit 3 (refill) | Follow-up (Visit 4) | Visit 5 (refill) | Final Study Visit (Visit 6) |

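### Each dispensing is 28 tablets but visits are 30 days apart, so on the scheduled days a fully adherent woman gives the month-6 urine sample 3 days after her last dose

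*Protocol*

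**What the plan says.** Section 7.3.2 (Baseline Visit) has staff "provide 28 (1 month) days of emtricitabine/tenofovir disoproxil". Section 7.3.3 (Refill Visit 1) says "Provide additional 28-days (1 month) supply of medication to the participant", and each later visit through the Final Study Visit in 7.3.4 carries the same quantity. The schedule of events (7.3.6) agrees: "Provide 28 days of emtricitabine/tenofovir disoproxil", marked at Visits 0 to 6. Section 6.1.5 sets the dose at one tablet, "once daily taken orally with or without food".

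Visits are on Days 30, 60, 90, 120, 150 and 180, each with a window of 7 days either side. Urine tenofovir is tested at months 2 and 6, and the month-6 level is primary endpoint 2. Section 4.3.1 justifies that measure as showing recent adherence, "thus whether the participant is currently using the drug". Section 10.5.2 analyses it as a log-transformed continuous level.

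No overlap stock is described, and section 9.3 states that PrEP cannot at present be obtained in Tanzania by another route. Section 6.1.2, on the product, describes a "bottle or blister pack of 30 film-coated tablets". No dispensing instruction uses 30.

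**The concern.** Twenty-eight tablets cannot cover 30 days of daily dosing. The shortfall recurs at every interval, including the one that ends at the endpoint sample. Because the endpoint is a single level that depends on how recently a tablet was taken, running out shortly before the visit enters the outcome directly.

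On the scheduled days this can also reverse the ranking of adherence. A woman who takes all 28 tablets from Day 150 without a break doses last on Day 177. A woman who skips two days takes the same 28 tablets but can dose on Day 179, 1 day before the sample instead of 3. By the recency bands in section 4.3.3 (item 12), the perfect adherer falls in the 2-to-3-day band and the other woman in the 24-hour band.

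Apart from the endpoint, women enrolled because of their HIV risk have days without a dose that the dispensing rule itself creates.

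**Working it through.** **The plan's own figure.** The protocol gives no figure for time from last dose to sample. The nearest stated number is the sample size for this endpoint (9.3), which assumes 80 ng/mL under consistent adherence:

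- Per arm: 2 × (1.960 + 0.842)² × 0.6² / ln(80/60)² = 68.3, so 69 per arm and 138 in total, as tabulated at ICC 0.
- Design effect at ICC 0.02: 1 + ((1 + 0.24²) × 8.25 − 1) × 0.02 = 1.1545. Then 138 × 1.1545 = 159.3, which rounds up to 160, as stated in the text.

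So 160 reproduces. Its reference level presupposes consistent dosing, which the dispensing rule does not allow.

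**Scheduled days.** Inputs: 28 tablets on Days 0, 30, 60, 90, 120 and 150 (7.3.2, 7.3.3), one a day (6.1.5), samples on Days 60 and 180.

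- Last dose before month 6: 150 + 28 − 1 = Day 177; 180 − 177 = 3 days.
- Last dose before month 2: 30 + 28 − 1 = Day 57; 60 − 57 = 3 days.
- Tablets before month 6: 6 × 28 = 168, for Days 0 to 179 = 180 dosing days. The shortfall is 12, or 11 if the observed first dose is additional to the 28.
- If each refill is started the day after dispensing, the gap before each sample is 2 days.

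**Any in-window schedule.** The earliest final visit is Day 173, which needs 173 doses (Days 0 to 172). 173 − 168 = 5 missed, or 173 − 169 = 4 with a separate observed dose. No permitted timing avoids missed doses.

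**Spread across the windows (assumed timing).** A day-by-day stock count on simulated schedules, with leftover tablets carried over and visit days independent and uniform within the window:

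| Dispensing rule | Assumed timing | No tablets at Visit 6 | Missed the day before Visit 6 | Missed the day before Visit 2 |
|---|---|---|---|---|
| 28 per visit | ±7 days | 51% | 44–45% | 51–53% |
| 28 per visit | ±2 days | 88% | 74% | 76% |
| 30 per visit | ±7 days | 20% | 13% | 31–35% |
| 37 at baseline, then 30 | ±7 days | 7% | 0% | 0% |

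With 28 per visit and ±7 days, about 38% are sampled 3 or more days after the last dose. In the last row, the 7% are women who took their final tablet the day before the visit, so no dose is missed.

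**Why 37 then 30 suffices.** Before visit k the supply is 37 + 30(k − 1) = 30k + 7 tablets, which covers Days 0 to 30k + 6. The latest permitted day for visit k is Day 30k + 7, so no in-window schedule has an uncovered day.

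**The case against.** The strongest reply is that 28 days is loose wording for a month. The visit text equates the two, section 4.1 calls refills monthly, the product is packed in 30s, and nothing tells staff to take two tablets out of a pack. If whole packs are handed over, the scheduled-day gap disappears. This is plausible and limits how firmly one can predict practice. But 28 is written at every dispensing and in the schedule of events, so the text needs correcting on either reading. Packs of 30 alone still leave about 13% with a missed day just before the final sample under uniform ±7 timing.

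The second reply is that the 3-day figure belongs to one point in the windows. That is right: dispensing on Day 150 with a final visit on Day 178 puts the last dose 1 day before the sample, and under uniform ±7 timing about 62% are sampled 1 to 2 days after dosing. It does not remove the forced missed doses.

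The third reply is symmetry. Both arms follow the same rule, endpoint 2 is a comparison between arms, and no power loss or changed estimate has been shown. This stands, and it limits the severity. It is also fair that the documents do not say how much protection is lost over two or three days, so the uncovered days are described here only as days without a dose. Finally, the buffer covers the worst in-window case, which goes beyond closing the scheduled-day gap.

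**Conclusion.** The point holds and should be fixed. Followed literally, the dispensing rule makes uninterrupted daily dosing to month 6 impossible: 11 to 12 missed doses on the scheduled days, and at least 4 to 5 on any in-window schedule. On the scheduled days the endpoint sample falls 3 days after the last dose (2 if each refill starts the day after dispensing).

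These counts assume that a woman takes one tablet daily while stock lasts and has no other source. The percentages rest further on assumed visit timing: 44–45% with a missed day just before the final sample under uniform ±7, and 74% under ±2. The likely effect is a lower and noisier level in both arms. Bias between arms would arise only if workplace and facility visits fall differently within the windows, which the protocol does not show. The loss in ng/mL cannot be stated, because the protocol gives no urine elimination rate.

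**What to change.** In sections 7.3.2 to 7.3.4 and in the schedule of events, replace the 28-day quantity with one 30-tablet pack per visit, and add a reserve of at least 7 tablets at baseline. The pack alone closes the gap on the scheduled days; the reserve closes it across the windows. At each urine sample, record the date of the last dispensing and the tablets in hand, and report days without supply by arm descriptively.

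Cost before month 6: 37 + 5 × 30 = 187 tablets against 168, so 19 more per woman. For 160 women that is 3,040 tablets, about 101 packs of 30. Including the dispensing at Visit 6, which comes after the endpoint, the totals are 217 against 196: 21 more per woman, or 3,360 tablets. If whole packs are already handed out, only the reserve is new. The 7-tablet reserve means splitting a pack or giving a second one at baseline. Pill counts are already planned (6.1.10, 7.1.1), so only the dispensing date needs confirming as a data field.

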### **7.3.3 FOLLOW-UP**

#### **Refill Visit 1 (Visit 1 Day 30 +/- 7; Month 1)**

- Provide additional 28-days (1 month) supply of medication to the participant
- Check on adverse effects
- Adherence Counselling
- Test for HIV

#### **Follow-up Visit 1 (Visit 2, Day 60 +/- 7; Month 2)**

- Record adverse events as reported by participant or observed by investigator.
- Record vital signs, results of screening for Syphilis or other health conditions.
- Conduct urine tests TDF testing for adherence.
- Provide additional 28-days (1 month) supply of medication to the participant
- Record participant's adherence to treatment program.

- Re-counsel the participant on adherence to emtricitabine/tenofovir disoproxil and need to contact the study if any changes in health arise.
- Visit 2 will require between 1.5 and 2 hours to complete

#### **Refill Visit 2 (Visit 3, Day 90 +/- 7; Month 3)**

- Provide additional 28-days (1 month) supply of medication to the participant
- Check on adverse effects
- Adherence Counselling

#### **Follow-up Visit 2 (Visit 4, Day 120 +/- 7; Month 4)**

- Record adverse events as reported by participant or observed by investigator.
- Record vital signs, or other health conditions.
- Conduct HTC including a rapid HIV test.
- Provide additional 28-day (1-month) supply of medication to the participant
- Record participant's adherence to treatment program.
- Re-counsel the participant on adherence to emtricitabine/tenofovir disoproxil and need to contact the study if any changes in health arise.
- Visit 4 will require between 1.5 and 2 hours to complete

#### **Refill Visit 3 (Visit 5, Day 150 +/- 7; Month 5)**

- Provide additional 28-days (1 month) supply of medication to the participant
- Check on adverse effects
- Adherence Counselling

---

### **7.3.4 FINAL STUDY VISIT**

#### **Final Study Visit (Visit 6, Day 180 +/- 7; Month 6)**

- Record adverse events as reported by participant or observed by investigator.
- Record vital signs or other health conditions.
- Collect blood for creatinine and syphilis testing.
- A point-of-care Hepatitis B surface antigen (HBsAg)
- Collect urine for TDF testing for adherence

- Test for HIV
- Record participant's adherence to treatment regimen.
- Provide additional 28-days (1-month) supply of medication to the participant
- Provide final HIV prevention counselling to participant.
- Conduct endline questionnaire
- Inform of continued follow-up support to care by the national program
- Visit 6 will require between 1.5 and 2 hours to complete

### 7.3.5 EARLY TERMINATION VISIT

At an early termination visit, if the participant is willing, all the above procedures and evaluations conducted for a final study visit will be conducted.

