### **5.4 Participant Withdrawal or termination**

#### **5.4.1 Reasons for Withdrawal or Termination**

Participants are free to withdraw from participation in the study at any time upon their requests and on their will without being forced or intimidated. The participants will be given clear explanation on the study, process and all procedures that will be done. The issue of withdrawal will be explained clearly that they can stop to participate in the study at any time and that their

withdrawal from the study will have no influence on how they will be treated or handled afterwards.

An investigator may terminate participation in the study (i.e. stop provision of PrEP) if:

- A participant tests positive for HIV
- A participants' renal function drops abnormally low
- Any clinical adverse event (AE), laboratory abnormality, or other medical condition or situation occurs such that continued participation in the study would not be in the best interest of a participant
- A participant ceases to work as a barmaid in Dar es Salaam

Apart from the above reasons for withdrawal or termination of participation in the study, the informed consent has a component that explains about stopping participation and that it will not impose any penalty to the participant.

---

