## **7. STUDY PROCEDURES AND SCHEDULE**

### **7.1 Study Procedures/Evaluations**

#### **7.1.1 STUDY SPECIFIC PROCEDURES**

- A medical history of each participant will be taken by clinicians at the sites. The history will include medication history including whether they are taking any over-the-counter medications. Based on this the Tanzanian healthcare provider will assess if they are taking any proscribed medications per WHO recommendations.

- A brief physical examination for vital signs, including height, weight and blood pressure will be completed by the clinical team.
- The clinical team will collect a finger-prick blood sample for point-of-care HIV and Hepatitis B surface antigen testing; , TDF testing for PrEP adherence, and will conduct a blood draw for laboratory-based serum creatinine, and syphilis testing.
- The results of all rapid tests will be provided to study participants at the time of testing. Serum creatinine tests will be discussed with participants if the results are abnormal.
- Standard HIV counselling will be provided to participants whether they test positive or negative, per national Tanzanian guidelines.

Adherence to emtricitabine/tenofovir disoproxil will be measured in three ways at each two-monthly visit. First, by self-reported adherence in terms of percentage of doses taken at the agreed time of day on the correct day. Second, by pill count of returned pills at the visit. Third, by a point-of-care urine assay for TDF. Patient-reported outcomes will be ascertained through a short questionnaire at each trial visit, in addition to the collection of baseline data prior to enrolment.

---

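### Section 7.3.5 carries the final visit's 28-day PrEP supply into the early termination visit without exception, while 5.4.1 treats investigator termination as stopping PrEP provision

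*Protocol*

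**What the plan says.** Section 7.3.5 of the Protocol consists of one sentence. Provided the participant is willing, at an early termination visit "all the above procedures and evaluations conducted for a final study visit will be conducted".

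The list it points to, in 7.3.4, includes "Provide additional 28-days (1-month) supply of medication to the participant". The schedule of events in 7.3.6 agrees: its row "Provide 28 days of emtricitabine/tenofovir disoproxil" is marked at the final visit. The table has no column for early termination.

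Section 5.4.1 states: "An investigator may terminate participation in the study (i.e. stop provision of PrEP) if" one of four conditions holds. These are a positive HIV test; abnormally low kidney function; an adverse event, laboratory abnormality or other medical situation that makes continuing against the participant's interest; and leaving bar work in Dar es Salaam.

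**The concern.** An early termination visit is the visit that a woman stopped under 5.4.1 would attend. For her, one section ends provision of the drug and another provides a further month of it.

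The hazards are ones that the protocol itself names. Section 2.4.1 lists drug resistance in women who take PrEP while HIV positive, and new or worsening kidney impairment. It presents HIV testing as the safeguard against resistance. That safeguard works only if the result decides whether pills are issued.

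The person issuing the pills also need not be the prescriber. Under 4.1, nurse counsellors issue pills at the facilities, and community-based providers give refills at the bars. Such staff might reasonably work from the visit list.

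**Working it through.** No formula or published figure is involved, so the check sets the sections side by side.

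1. **Does 7.3.5 contain a clinical exception?** No. Its only condition is the participant's willingness. That is consent, and it does not depend on why she was stopped.

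2. **Could the procedures it refers to mean assessments only?** No. The schedule in 7.3.6 lists dispensing in its procedures column, and 7.3.5 takes over all final-visit procedures.

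3. **Does another section supply the exception?**
   - 5.4.2 (handling of withdrawals) keeps women who discontinue PrEP but remain eligible in follow-up. It gives no rule on dispensing.
   - 6.1.8 (dose modifications and delays) has no entry other than none.
   - 7.3.6 has no footnote on the dispensing row.
   - 4.1 says that the team will actively follow up to take women off PrEP for side effects or, in the workplace group, also for other exclusion criteria. Under 5.2, those criteria include a positive HIV test and low renal function. This shows the intent but does not mention the early termination visit.

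4. **Which women are caught?** Those terminated for any of the four reasons in 5.4.1. Three of the reasons are clinical, and there the supply is a potential hazard. The fourth, leaving bar work, is not clinical, but the conflict of wording is the same because 5.4.1 equates termination with stopping PrEP for all four. One further case follows from the list itself: the final visit includes an HIV test, so a woman who attends for another reason could test positive at that visit.

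5. **How much drug is at issue?** The supply covers 28 days and the dose in 6.1.5 is one tablet daily: 28 × 1 = 28 tablets per affected woman. The protocol gives no rate of positive HIV tests or of renal stops during follow-up, so the number of affected women is not estimated.

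**The case against.** The strongest reply is that the stop rule is already clear. Section 4.1 commits the team to discontinuing women with side effects or exclusion criteria and leaves prescribing to a clinician. Section 11.4.2 promises immediate referral for treatment after a positive test. Section 5.4.1 says only that the investigator may terminate, with the reference to PrEP in brackets, and the evident purpose of 7.3.5 is to collect final-visit data. On that view a specific stop rule overrides a general cross-reference.

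Most of this stands. The intent is plain, and it makes the point a drafting conflict rather than a plan to treat women who have seroconverted. It does not remove the conflict, because none of these sections says that drug is withheld at an early termination visit. Section 10.3 counts any noncompliance with the protocol as a deviation, so staff who correctly withheld the pills would, on the wording, be departing from 7.3.5.

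A reader might go further and infer that the scheduled lists contain the same contradiction, since they also pair an HIV test with a supply. At Month 4, for example, "Conduct HTC including a rapid HIV test" stands beside "Provide additional 28-day (1-month) supply of medication to the participant", and Months 1 and 6 have the same pairing. The documents do not support that reading. Those lists describe visits of women continuing on PrEP, and a list that does not repeat the stop rule does not contradict it. Section 5.4.2 expects women who have discontinued PrEP still to be invited to scheduled visits, which implies visits without dispensing. Counting such pairings would not measure risk either. It would also depend on which HIV test schedule is used: 2.4.1 gives baseline and Months 2 and 4, 4.1 links testing to two-monthly follow-up visits, and 7.2 and 7.3.6 give Months 1, 4 and 6 after screening.

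**Conclusion.** The point holds as a minor internal inconsistency in safety wording, confined to 7.3.5 (with the final-visit list that it imports) against 5.4.1. Its size is one 28-day supply per affected woman if the text is followed literally.

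This rests on reading the final-visit procedures to include dispensing, which the schedule table supports. It also rests on taking the bracketed words in 5.4.1 at face value.

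A reader might infer that the trial would knowingly supply PrEP to HIV-positive women, or that the adherence endpoint is compromised. Neither follows. Section 4.1 points the other way on the first, and nothing here changes an endpoint definition, the sample size, power or type I error. Visit procedures belong in the protocol, so a statistical analysis plan would not be expected to settle the matter.

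**What to change.** Add to 7.3.5: *except that study drug is not dispensed to a participant whose PrEP has been stopped under 5.4.1 or who tests HIV positive at that visit; HIV-positive women are linked to the CTC.*

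Then decide the non-clinical case. If a bridging month is intended for women who only left bar work, 5.4.1 must say so as well. Otherwise its equation of termination with stopping PrEP still contradicts the supply. If no bridging month is intended, link these women to the national PrEP programme, as 7.8 already provides at study closure.

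The cost is one clause, and possibly a second in 5.4.1. No visit, test or participant is added. The HIV condition should add little or no wait, because under 7.1.1 "The results of all rapid tests will be provided to study participants at the time of testing". Staff need only read that result before issuing pills.
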